**Definition of Serious Adverse Events (SAE).**
* The Serious Adverse Events (SAE) are defined as any unfavorable medical occurrence that meets one or more of the following criteria:

Results in the participant's death.Poses a life-threatening risk to the participant's well-being.Requires hospitalization, including cases where it extends an ongoing hospital stay.Leads to persistent or significant disability or incapacity.Involves a congenital anomaly or birth defect.

Additionally, other "important medical events" may also be considered serious adverse events if, based on appropriate medical judgment, they have the potential to jeopardize the participant's health and necessitate medical or surgical intervention to prevent any of the outcomes mentioned above.

It is important to note that the term "life-threatening" within the definition of "serious" pertains to events where the participant was at risk of death at the time of the occurrence. It does not refer to events that hypothetically might have caused death if they were more severe.

All SAEs (including a site investigator causality assessment) should be reported by the site to the sponsor within 24 hours of the site becoming aware of the event and their causal relationship to tecovirimat (or other antivirals) are assessed. The Sponsor reviews all SAE reports received and conducts the causality and expectedness assessment of the event. Additional information (including the reason for considering the event both serious and related, and relevant medical and medication history) may be sought from the reporting site. The expectedness assessment considers Section 4.8 of the EMA Summary of Product Characteristics (SmPC) as Reference Safety Information for tecovirimat. Where possible, Section 4.8 of the relevant EMA SmPC is also used to assess the expectedness of the event for any other antiviral used in the study. The Sponsor conducts a causality and expectedness assessment within one business day of receiving the SAE report to determine whether the event is an SAE, SAR or SUSAR. In the event of divergent causality assessments by the site investigator and the Sponsor, both assessments are recorded and the assessment determining the strongest relationship defines the event as a SAE or SAR.

If there is a reasonable probability that any SAE is caused by tecovirimat or any other antiviral medication, it is considered a Suspected Serious Adverse Reaction (SSAR).

Participants who encounter a SAR or SSAR, which are events deemed to be associated with the treatment, will be followed up until the event is resolved.

All SUSARs are reported to:

The EMA by the Sponsor’s Representative in the EU within seven days, if the event is fatal or life-threatening, or otherwise 15 days.The UK Research Ethics Committee (REC) within 15 days of becoming aware of the eventThe responsible ethics committee and SwissMedic in Switzerland within seven days, if the event is fatal, or within 15 days for all other events.
*Note:* All SAEs resulting in death are reported to the ethics committee and SwissMedic within seven days.The Domain Specific Review Board (DSRB) by the Sponsor’s Representative in Singapore within seven days.

In countries where the study is considered an observational study, it is the responsibility of the treating clinician to report (serious) AE directly to national and regional regulatory bodies according to applicable national and regional legislation i.e., the MHRA’s Yellow Card system in the UK.

Please see ‘Appendix G, Additional File 2’ in
*Extended data* for full details of the SAE reporting process for the study
^
7
^.

There may also be additional country specific requirements for safety reporting depending on regulatory requirements, in particular, the additional requirements for the EU/EEA are found in Appendix H, Additional File 2 “safety reporting for EU/EEA sites” section”.

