### Outcomes

**
*Primary outcome measure.*
** The primary outcome measure of this study is the participant’s time to lesion resolution without any serious complications. Lesion resolution is the first day on which all lesions are resorbed, scabbed or desquamated and mucosal ulcers healed. Lesion resolution is assessed until a maximum of 14 days since the date that the diagnostic sample is taken (for participants who do not receive mpox-specific antiviral treatment) or the day of treatment initiation (for participants who receive mpox-specific antiviral treatment).

**
*Secondary outcomes.*
** Secondary outcome measures evaluate clinical and virologic outcomes. Clinical outcomes are assessed on the basis of:

1. Clinical status on day 14 and day 28 according to a four-point ordinal scale assessed by a physician or a study nurse. The ordinal scale is a) all lesions are resolved and no serious complications, b) active lesions and no serious complications, c) serious complication and/or hospitalization due to mpox, or d) death.2. Evidence of recrudescence or relapse at day 60 and day 180.

*Note:* A "serious complication" is any complication associated with a Serious Advent Event (SAE) that is life-threatening, results in hospitalisation, prolongation of existing hospitalisation, disability, incapacity, or a congenital anomaly; or any other complication that is considered medically significant.

Virologic outcomes in Tier 1 are assessed on the basis of:

1. Change from baseline in mpox virus DNA levels in throat swabs on days 4, 8, 14 and 28.2. Change from baseline in mpox virus DNA levels in blood on days 4, 8, 14 and 28.3. Presence of mpox virus DNA in lesion swabs on days 4, 8, 14 and 28.

The study also assesses the number and type of SAEs, Suspected Adverse Reactions (SARS) and Suspected Unexpected Serious Adverse Reactions (SUSARs) within 28 days of enrolment.

Pregnancy outcomes defined as the final known health status of the mother and child are evaluated in any participants who are pregnant during the course of the study.

**
*Exploratory outcomes in Tier 2 and Tier 3.*
** Further virologic and immunological outcomes are also evaluated in France under this protocol to learn more about viral transmission, humoral and cellular immune responses. The outcome measures are as follows:

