1&2	HIV-RNA quantification						X		X
1&2	MPXV quantification (sPCR) + infectivity assessment (cell culture)	X	X	X	X	X	X	X	X
1&2	MPXV sequencing	X	X	X	X	X	X	X	X
1&2	Humoral immune response characterisation (anti- MPXV antibodies quantification, seroneutralization)						X		
1&2 &3	Cellular immune response characterisation						X		
1&2	Genetic host factors determination + auto-immune antibodies detection						X		
1&2	Tecovirimat pharmacokinetics						X		

HIV, human immunodeficiency virus; MPXV, mpox virus.

Please refer to ‘Additional File 2: Appendix F’ in
*Extended data* for further information on sample processing, analysis and storage in the UK
^
7
^.

**
*Participant self-assessment survey.*
** All participants are asked to complete a self-assessment survey from the point of entry into the study until D180
*via* a secure online questionnaire. The questionnaire, completed
*via* online REDCap survey, captures information about the participant’s signs and symptoms, including lesion status.

For Tier 2 and Tier 3 in France, the baseline self-assessment survey includes an additional social and sexual behaviour questionnaire.

**
*Outcome assessment.*
** During the medical assessment on D14, 28, 60 and 180, the clinical status according to a four-point ordinal scale (see the
*Outcomes* section) is recorded.

For participants who are pregnant at any time during the study, they are followed in the study until their pregnancy outcome is known.

*Note:* As participants can consent to enrol in the study at any point after receipt of a positive PCR result for mpox infection, the eCRF can be completed using existing medical notes and results of samples already taken.

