### Harms

**
*Safety reporting.*
** The assessment of safety outcomes—a study objective—requires adverse event reporting, serious adverse event reporting and collection of pregnancy outcomes in both treated and non-treated cohorts.

The study procedures carry minimal risk and therefore AE related to the study procedures are not anticipated.

AE and SAE data are collected in the eCRF from the date that the participant’s diagnostic sample for mpox infection was collected or the date of enrolment (whichever comes first) until D28.

*

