## Study status

The current version of the protocol is version 2.0, dated 25 November 2022. The study was authorised for the first time in Switzerland on 22 June 2022, and is due to end on 31 January 2024.

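### A congenital anomaly is defined as an SAE, but the stated SAE window closes at D28, and no text shown carries an anomaly found later in pregnancy follow-up into SAE handling

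*Protocol article*

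**What the plan says.** All references are to the protocol article.

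- **Definition of Serious Adverse Events (SAE).** One criterion is that the event "Involves a congenital anomaly or birth defect". The note on serious complications under Outcomes also names a congenital anomaly.
- **Harms, Safety reporting.** "AE and SAE data are collected in the eCRF from the date that the participant’s diagnostic sample for mpox infection was collected" or, as the alternative start, "the date of enrolment (whichever comes first) until D28". Pregnancy is not excepted. The opening sentence of the section names pregnancy outcomes as a further component of safety assessment, next to AE and SAE reporting.
- **Outcomes.** The safety outcome is the number and type of SAEs, SARs and "Suspected Unexpected Serious Adverse Reactions (SUSARs) within 28 days of enrolment". The safety paragraph under Statistical methods repeats the limit.
- **Data collection methods, Medical assessments.** Assessments at baseline, D14, D28, D60 and D180 record AE and SAE details, with no cut-off at D28.
- **Pregnancy.** Outcomes has "Pregnancy outcomes defined as the final known health status of the mother and child". Data collection methods says of pregnant participants that "they are followed in the study until their pregnancy outcome is known". Definition of end of study is worded to match.

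**The concern.** The article plans to watch each pregnancy to its end and classes one possible finding, a congenital anomaly, as an SAE. Yet it closes the stated SAE window long before most of those pregnancies end. The 24-hour report to the sponsor, the causality and expectedness assessment, the route to a SUSAR and the medical monitor's review all attach to SAEs. A pregnancy outcome is defined only as a health status, and none of these steps is attached to it.

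Congenital anomaly is also the one SAE criterion that plainly reaches the child. The death and life-threatening criteria are worded in terms of the participant, so stillbirth and neonatal death are not clearly covered. If the D28 limit is applied as written, the SAE tables would contain almost no anomalies recognised at birth. A reader could take that as reassurance when it reflects only the length of the window. Pregnancy is not an exclusion criterion, safety is a stated objective, and the Introduction says tecovirimat was approved under exceptional circumstances without a clinical efficacy trial.

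**Working it through.** The article gives no figure on this point, so there is none to reproduce. The check is date arithmetic plus a comparison of sections.

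**Inputs**
- SAE window ends at D28 (Harms), or at D180 if the assessments in Data collection methods govern.
- Permitted visit windows: ±2 days at D28 and ±7 days at D180 (Table 1).
- Pregnancy length is not in the documents. I assume 40 weeks (280 days), with a range of 37 to 42 weeks (259 to 294 days).
- The anomaly is assumed to be first recognised at birth.

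**Formula.** Day D is D − 1 days after D1. The least gestational age on D1 for birth to fall by day D is (term in days − (D − 1)) / 7 weeks.

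| SAE window ends | 40-week term | With visit window | Term 37 to 42 weeks |
|---|---|---|---|
| D28 | (280 − 27)/7 = 253/7 = 36.1 weeks | 35.9 to 36.4 | 232/7 = 33.1 to 267/7 = 38.1 |
| D180 | (280 − 179)/7 = 101/7 = 14.4 weeks | 13.4 to 15.4 | 80/7 = 11.4 to 115/7 = 16.4 |

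Thus a pregnancy at 12 weeks on D1, with birth at 40 weeks, ends 28 × 7 = 196 days later, on D197. That is after both cut-offs. Settling the conflict in favour of D180 would therefore still leave out most first-trimester exposures.

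**The sections compared**
1. Harms stops SAE collection at D28, while Data collection methods records SAE details at D60 and D180. Both cannot describe the same eCRF.
2. Day numbers run from the diagnostic sample, or restart when treatment begins later, whereas the safety outcome runs 28 days from enrolment. Enrolment may follow D1, so the two limits need not end on the same day.
3. Pregnancy follow-up has no day limit, so the child's health status is collected at any gestational age.
4. Nothing shown links item 3 to the SAE process once the SAE window has closed.

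**The case against.** Much of the case on the other side is right, and it limits the point. A reader might infer that an anomaly after D28 is never recorded, reported or assessed. The documents do not support that.

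- **Recorded.** Pregnancy outcomes are a named part of safety reporting, cover mother and child, and have no D28 limit. A 28-day SAE count beside a separate pregnancy outcome is a possible design.
- **Reported and assessed.** The D28 limit concerns data entered in the eCRF. The 24-hour duty covers all SAEs, runs from site awareness and has no calendar limit. Where the study is observational, treating clinicians report directly to regulators. Appendices G and H hold the SAE process and the EU/EEA requirements. They are not shown and may contain a pregnancy rule.
- **D28 for everyone.** The D60 and D180 assessments say otherwise, and D28 moves when D1 restarts at late treatment.
- **End date.** A reader might also infer that follow-up is cut off because Study status says the study "is due to end on 31 January 2024". That is a forecast. Definition of end of study already waits for the pregnancy outcome, so no change is needed there.
- **Size.** Anomalies detected before birth may fall inside the window. By the Introduction, the outbreak mostly affected men who have sex with men. The Discussion counts 55 + 7 + 2 = 64 participants of 601 treated with tecovirimat, cidofovir or both, and reports no pregnancy.

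Two things still stand. The visible text gives two different SAE windows. It also defines an event as an SAE while closing the stated window before that event would usually be recognised. These are rules that the article states, so the point does not depend on detail left to another document.

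**Conclusion.** The point holds in a limited form. As written, the SAE definition and the SAE window do not fit together for congenital anomalies, and the article contradicts itself on when SAE collection ends. Assuming a 40-week term and recognition at birth, the D28 window captures an anomaly only when the pregnancy is at about 36 weeks or more on D1 (33.1 to 38.1 for terms of 37 to 42 weeks). Under the D180 reading the threshold is about 14 weeks (11.4 to 16.4).

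Later anomalies are kept as pregnancy outcomes. What the visible text lacks is any step from there into SAE reporting, assessment and counting, and the unseen appendices may supply it. The consequence is for safety-signal capture and for how the SAE tables are read. No effect estimate is touched, and the number of pregnant participants, which is not given, is probably small.

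**What to change.** 1. Reconcile Harms, Definition of Serious Adverse Events, Data collection methods, Outcomes and the safety paragraph of Statistical methods on one SAE window: when it starts, when it ends, and what the D60 and D180 assessments record.
2. Add to Harms, Safety reporting, a sentence to this effect: for participants pregnant during the study, a congenital anomaly or other serious pregnancy outcome found during the planned follow-up is recorded, reported and assessed as an SAE until the outcome is known. These events are listed separately from the 28-day counts, so that those counts keep a common window for all participants.
3. If Appendix G or H already contains such a rule, a cross-reference in Harms is enough for item 2.

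The follow-up is already planned, so the added work is an SAE form when an event occurs. The amendment is minor but still needs approval by the responsible ethics committees, and the Discussion mentions 10 participating countries. Since enrolment has stopped, the gain is in pregnancies still open and in how outcomes already known are classified and reported.

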### Frequency and plans for auditing trial conduct

No audit of the conduct of this programme is planned.

## Plans for communicating important protocol amendments to relevant parties (
*e.g.*, trial participants, ethical committees)

All amendments to the protocol are reviewed and approved by the responsible ethics committees before implementation.

## Dissemination policy

The results of this study are expected to be published in open-access peer-reviewed literature and presented at scientific conferences. A lay summary of the results will also be made available.

### Dissemination policy—Authorship eligibility guidelines

The Investigators will be involved in reviewing drafts of the manuscripts, abstracts, press releases and any other publications arising from the study. Authors will acknowledge that the study was funded by Wellcome, The Bill and Melinda Gates Foundation and for EU/EEA countries: MPX-Response. Authorship will be determined in accordance with the ICMJE guidelines and other contributors will be acknowledged.

## Dissemination policy—Public Access

A summary of the results will be made available in the publicly-facing EU CTIS platform within one year following the last visit of the last participant in the last participating EU country. A summary of the global results, if available later, will also be provided.

## Discussion

Observational studies are an integral part of a multi-pronged clinical research approach alongside interventional trials. They can rapidly generate solid evidence on clinical characterisation and outcomes, especially with a new emerging disease, such as the ongoing mpox clade IIb/III outbreak, and thus inform both practice and clinical trials design. However, in order for them to be successful, a number of criteria need to be fulfilled.

One is speed. MOSAIC got off to a fast start, recruiting the first patient in Switzerland on 4 July 2022, just two months after the start of the outbreak, but by October 2023 only six of the 10 participating countries have enrolled participants either prospectively or retrospectively. This is because most of the EU participating countries received approval only when the number of cases was already dropping and then faced contractual issues.

A detailed report of the various hurdles encountered has been shared with the European Medicines Agency (EMA), summarised in a paper for wider dissemination
^
10
^.

For evidence generation in health crises, we need a conducive regulatory and political environment, allowing shorter approval timelines and simplification of administrative regulation
^
10
^. Unfortunately, the MOSAIC experience shows that the system, at least in the European Union, is not ready. Countries where the study is considered as observational where able to start quickly (between, 13 and 20 days after the initial submission) Switzerland enrolled the first case on 4 July 2023 after a two-week review process, quickly followed by France that had an initial approval as observational study, and then the UK. In comparison, in the other European Union participating countries, the median time to decision was 46.5 days (IQR 41 to 62)
^
10
^. An additional complication has been that tecovirimat—the only drug currently licensed for treating mpox in the EU and UK—has been available only in small quantities, and mostly through donations by the manufacturer, SIGA, when cases were peaking, and through a centralised purchase in the EU only much later (end of September 2022).

Beyond the operational aspects, starting clinical research for under-researched diseases like mpox is often slowed down by the lack of established methodologies for defining outcomes and endpoints to assess the disease and the treatment effect. MOSAIC benefitted from the tecovirimat Expanded Access Programme (EAP) protocol underway in the Central African Republic (CAR), which could be quickly adapted to the clade IIb
^
6
^, and from experience with
clinical characterisation protocols. Outcomes have also further been harmonised across several other studies and trials currently running or planned on mpox: randomised clinical trials of Tecovirimat (
Platinum in the UK (ISRCTN17461766) and in Canada (NCT05534165), Unity in Switzerland, Brazil and Argentina (NCT05597735), Stomp (NCT05534984), EPOXI in Europe, PALM007 in Democratic Republic of Congo (NCT05559099), MOSA in Africa), EAPs (the US Army EAP (NCT02080767) and the Tecovirimat for mpox in Central African Republic (ISRCTN43307947)), the WHO Monitored Emergency Use of Unregistered and Investigational Interventions (MEURI) and observational studies (the
Clinical Characterisation Protocol in UK and Netpox in Brazil (NCT05784038)). So that now hopefully consistent, comparable evidence will be generated, although some methodological questions are still unresolved
^
11
^. At the same time, uncertainties persist about outcomes and study endpoints, both clinical and virologic
^
11
^. For instance, current studies, including MOSAIC, tend define lesion resolution as “For skin lesions, typically this means the lesion has scabbed, desquamated and new layer of skin has been formed. For mucosal lesions, the phase of scabbing and desquamation is absent, and healing with new layer of skin ensues.” (UNITY trial) or “skin lesions are scabbed, desquamated or healed, and visible mucosal lesions are healed” (STOMP trial). However, there appear to be substantial inter-observer differences in lesion classification
^
12
^, and we know that the MPXV persists in scabs in both clade I and II cases
^
13
^. It will therefore be important for future studies to more consistently standardise definitions and lesion assessment.

Then, beyond speedy set-up, there is also the need for sustainability, so that information can be accrued during protracted outbreaks, or such as ‘dormant’ protocols are maintained in-between outbreaks and can be quickly restarted as needed. Luckily, the current mpox outbreak has been curbed. At the time of writing, MOSAIC has enrolled 601 PCR-confirmed mpox cases of whom 55 treated with tecovirimat, 7 with cidofovir and 2 with both. Enrolment has been stopped and the last follow up visits are expected in January 2024. Partial results on the first 122 cases have been communicated earlier in 2023
^
14
^.

Lastly, community outreach and integration of patients views into protocol design and communication should be integral to clinical research, especially when it concerns stigmatising conditions
^
15
^.

## Study status

The current version of the protocol is version 2.0, dated 25 November 2022. The study was authorised for the first time in Switzerland on 22 June 2022, and is due to end on 31 January 2024.

## Declarations

### Research ethics approval

**
*Ethical and regulatory considerations.*
** The Investigator ensures that this study is conducted in accordance with the principles of the Declaration of Helsinki.

**
*Approvals.*
** Following Sponsor approval, the protocol, informed consent form, participant information sheet and any patient-facing materials material have been submitted to an appropriate Research Ethics Committee (REC) for each jurisdiction, and Health Research Authority (HRA) and host institutions for written approval.

The Investigator has submitted and, where necessary, obtained approval from the above parties for all substantial amendments to the original approved documents.

**
*Reporting.*
** The Chief Investigator at the Sponsor or the Sponsor’s Representative (where applicable) shall submit once a year throughout the study, or on request, an Annual Progress report to the approving RECs, HRA (in the UK), host organisation, Sponsor and funder (where required). In addition, the start date of the clinical trial, inclusion date of the first subject, end of recruitment and end of the clinical trial for each member states and globally.

In addition, an End of Study notification and final report will be submitted to the same parties.

